## 6 DRUG INFORMATION AND DOSE MODIFICATIONS

### 6.1 Drug information

The investigational drug Peg-Interferon alpha-2b is available as „PegIntron 50/-80/-100/-120/-150 µg powder inclusive solution within an injector pen. In the event that the pen is not used, the sponsor will provide PEG2b in vials (and sterile water for injection) that allow for dosing equivalent to the pen. Ribavirin is available as „Rebetol 200 mg capsules“. Both drugs are licensed in the European Union (EU) by MSD Sharp & Dohme GmbH. PegIntron® is an interferon alpha-2b molecule conjugated with a 12kDa polyerthylene glycol moiety. The characteristic of this formulation is a longer half-life and an improved pharmacokinetic profile compared to the interferon alpha-2b molecule. This allows for a once weekly subcutaneous injection.

Rebetol® is given orally on a daily basis in combination with interferon alpha therapy.

PEG-Interferon alfa-2b (PegIntron®) and Ribavirin (Rebetol®) are approved for the treatment of chronic hepatitis C. Detailed information is given by the Summary of Product Characteristics (SmPC; “Fachinformation”).

### 6.2 Dosage of investigational drugs

**PEG-Interferon alpha-2b (PegIntron®)** will be given as a subcutaneous injection once weekly weight adjusted as follows#:

| Body Weight | Dose   | Pen or Vial Strength (µg) | Injection Volume (ml) |
|-------------|--------|---------------------------|-----------------------|
| 40-43 kg    | 60 µg  | 100 µg                    | 0,3                   |
| 44-50 kg    | 70 µg  | 100 µg                    | 0,35                  |
| 51-56 kg    | 80 µg  | 100 µg                    | 0,4                   |
| 57-63 kg    | 90 µg  | 100 µg                    | 0,45                  |
| 64-68 kg    | 100 µg | 100 µg                    | 0,5                   |
| 69-75 kg    | 105 µg | 150 µg                    | 0,35                  |
| 76-85 kg    | 120 µg | 150 µg                    | 0,4                   |
| 86-95 kg    | 135 µg | 150 µg                    | 0,45                  |
| ≥ 96 kg     | 150 µg | 150 µg                    | 0,5                   |

# the body weight prior to the ongoing standard therapy defines the dosing

**Ribavirin (Rebetol®)** will be given as capsules weight adjusted daily as follows#:

| Body weight | Dose   | Capsules/
daily intake |
|-------------|--------|---------------------------|
| < 64 kg     | 800 mg | 2-0-2                     |

|          |         |       |
|----------|---------|-------|
| 65-75 kg | 1000 mg | 2-0-3 |
| 76-85 kg | 1000 mg | 2-0-3 |
| >85 kg   | 1200 mg | 3-0-3 |
| >105 kg  | 1400 mg | 3-0-4 |

# the body weight prior to the ongoing standard therapy defines the dosing

## 7 SAFETY ISSUES

### 7.1 Warnings and Precautions

No evidence is available at the time of the completion of the study protocol to the Hep-Net Study Group indicating that special warnings or precautions were appropriate, other than those noted in the SmPC.

### 7.2 Adverse Events

An adverse event (AE) is any untoward medical occurrence or unfavourable and unintended sign in a subject administered a pharmaceutical product/biologic (at any dose), or medical device, whether or not considered related to the use of that product. Additionally, any event that is associated with or observed in conjunction with a product overdose (whether accidental or intentional) or a product abuse and/or withdrawal is also considered an adverse event.

All AEs encountered during the clinical study will be reported on the AE page of the Case Report Form (CRF). Intensity of adverse events will be graded on a four-point scale (mild, moderate, severe, life threatening) and reported in detail as indicated on the CRF.

The investigator must assess the relationship of any adverse event to the use of study drug, based on available information, using the following guidelines (Table 3):

Table 3. Guidelines for Assessing the Relationship of an Adverse Event to Treatment

|                   |                                                                                                                                                   |
|-------------------|---------------------------------------------------------------------------------------------------------------------------------------------------|
| Unlikely related: | no temporal association, or the cause of the event has been identified, or the drug, biological, or device cannot be implicated                   |
| Possibly related: | temporal association, but other etiologies are likely to be the cause; however, involvement of the drug, biological, or device cannot be excluded |
| Probably related: | temporal association, other etiologies are possible, but unlikely                                                                                 |

### 7.3 Serious Adverse Events

A serious adverse event (SAE) is any event that results in any of the following outcomes:

- is fatal
- is life-threatening (life-threatening is defined as the patient was at immediate risk of death from the AE as it occurred)
- is significantly or permanently disabling
- requires in-patient hospitalization, or prolongs hospitalization
- is a congenital anomaly or birth defect

Important medical events that may not result in death, be life-threatening, or require hospitalization may be considered a serious adverse drug reaction when, based upon appropriate medical judgment, they may jeopardize the patient or subject and may require medical or surgical intervention to prevent one of the outcomes listed in this definition. Examples of such medical events include allergic bronchospasm requiring intensive treatment in an emergency room or at home, blood dyscrasias or convulsions that do not result in inpatient hospitalization, or the development of drug dependency or drug abuse.

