### 3.2 Endpoints

Primary endpoint is

- Reduction of Relapse rate (HCV-RNA positive in serum by a standard HCV-PCR with a detection limit of at least 15 IU/ml) 24 weeks after the end of treatment and thus improvement of sustained virological response rates (SVR)

Secondary endpoints are

- Virological response rates (HCV-RNA negative in serum by a standard HCV-PCR with a detection limit of at least 15 IU/ml) at the end of therapy
- Biochemical responses as determined by ALT and AST levels at the end of treatment and at the end of follow up.
- Severity and frequency of adverse events (AE)
- Analysis of quality of life (with questionnaire SF-36)

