#### **7.4     *Reporting of SAE's***

Any SAE that occurs while treatment or aftercare whether or not deemed drug-related or expected, should be reported within 24 hours after knowledge by the treating physician to his/her local regulatory or drug safety reporting agency (Sponsor Hep-Net) along with a copy to MSD Sharp & Dohme GmbH, Division Pharmacovigilance. Also SAEs, that occur within 30 days after the last application of the study medication or within 30 days after the last medical check-up need to be reported. In case of pregnancy of a female patient in the study or of a female partner of a male patient participating in the study this must be handled in the same way – it must be reported as if it would be an SAE. If the pregnancy affects the female partner of a patient both data about the pregnancy and data about the treatment of the patient are regarded.

In any case the form for Reporting of an SAE is to be filled out and to be faxed to the following addresses within 24 hours after knowledge:

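### Section 7.3 classes important medical events as serious adverse drug reactions, while sections 7.2 and 7.4 keep adverse events and 24-hour SAE reporting independent of causality

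*Protocol*

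**What the plan says.** Four parts of the protocol bear on this point.

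- **Section 7.2** defines an adverse event "whether or not considered related to the use of that product". Relatedness is a separate assessment, made with Table 3 in three grades: unlikely, possibly and probably related. The lowest grade applies when there is "no temporal association, or the cause of the event has been identified, or the drug, biological, or device cannot be implicated".
- **Section 7.3, list.** "A serious adverse event (SAE) is any event that results in any of the following outcomes": death, threat to life, significant or permanent disability, hospital admission or its prolongation, and congenital anomaly. None of the five depends on causality.
- **Section 7.3, next paragraph.** Important medical events that may not cause death, endanger life or "require hospitalization may be considered a serious adverse drug reaction when, based upon appropriate medical judgment, they may jeopardize the patient" and may call for intervention to avert a listed outcome. The examples include convulsions and blood dyscrasias that do not lead to admission.
- **Section 7.4.** "Any SAE that occurs while treatment or aftercare whether or not deemed drug-related or expected, should be reported within 24 hours". The duty covers treatment and aftercare. It also covers the 30 days after the last dose or the last medical check-up.

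**The concern.** In this protocol *adverse event* is a causality-free term and *adverse drug reaction* is not. Section 7.3 uses the second term at the one place where sections 7.2 and 7.4 need the first. Important medical events are not on the list of five, and no other sentence makes them SAEs. Their only route to serious status runs through a phrase that presupposes attribution to the drug.

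Two things are at stake. The first is the sponsor's 24-hour safety information: events of this class that an investigator judges unrelated may never be sent. The second is consistency. The definition is applied locally at about 30 centres (section 3.1), and a literal reader and a lenient reader would classify the same event differently.

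**Working it through.** No sample size, power or rate is involved, and the protocol states no figure to reproduce. The check is a comparison of the texts followed by a worked case.

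**1. Is causality part of the rule?**

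| Place | What it governs | Causality condition |
|---|---|---|
| 7.2 | Definition of an AE | Excluded expressly |
| 7.3, list | Five SAE outcomes | None |
| 7.3, next paragraph | Important medical events | Implied by the label *drug reaction*; the stated tests are jeopardy and need for intervention |
| 7.4 | 24-hour SAE reporting | Excluded expressly |

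The third row is out of line with the other three.

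**2. Worked case.** Take a convulsion managed without admission, one of section 7.3's own examples, and suppose that it meets none of the five listed outcomes.

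| Table 3 rating | Clause read literally | Clause read loosely |
|---|---|---|
| Possibly or probably related | Can be serious | Can be serious |
| Unlikely related | Not an SAE, no 24-hour report | Can be serious, 24-hour report |

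The readings part in one cell: an important medical event, outside the five outcomes, rated unlikely related. That cell is the extent of the defect. The literal column also assumes that *possibly related* is enough to make an event a drug reaction. The protocol does not say which Table 3 grade is.

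**3. Could the defect fall unevenly on the arms?** From section 3.1:

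- Group A: 24 further weeks on drug + 24 weeks of follow-up = 48 study weeks.
- Group B: 12 further weeks on drug + 24 weeks of follow-up = 36 study weeks.

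In study weeks 13–24 Group A is on drug and Group B is in follow-up. Table 2 collects adverse events in follow-up and section 7.4 covers aftercare, so Group B's events in that window are in scope. One criterion for the lowest grade in Table 3 is the lack of a temporal association. The trial is open label, so the investigator knows who is on drug. On the literal reading, an off-drug event in Group B is then more open to an unlikely-related rating, and so to loss of serious status, than a like event in Group A. Each step is possible, but none is stated in the protocol, and there is no event rate from which to compute a size.

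**4. What is not touched?** Under section 7.2 every adverse event goes on the CRF and is graded on a four-point intensity scale. Whether an event is also called serious changes neither its count nor its grade. The secondary endpoint in section 3.2 concerns the severity and frequency of adverse events and does not name seriousness. The primary analysis in section 8.1 uses SVR only.

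**The case against.** The strongest reply is that the phrase is loose wording and not a causality gate. The paragraph stands under the heading for serious adverse events and refers back to the same definition. Its stated conditions are jeopardy to the patient and possible need for intervention. It does not invoke Table 3, and no sentence says that an unlikely-related rating takes an event out of the clause. This stands in part: the lenient reading is available and may well be what was meant. But the literal term points the other way, and a rule that triggers a 24-hour duty should not rest on which reading a site adopts.

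A reader might go further and infer that the same event would be serious in Group A and non-serious in Group B, and that the safety comparison is thereby biased against the longer course. The documents do not support that:

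- One definition and one reporting rule apply to both groups.
- The split needs the literal reading, an event outside all five outcomes, a date in study weeks 13–24, an unlikely-related rating in Group B, and a related rating for the matching event in Group A.
- Being off drug is not the same as lacking a temporal association. Section 7.2 counts events associated with product withdrawal as adverse events, and section 7.4 keeps a 30-day window after the last dose. Early off-drug events could well be rated possibly related.
- Group A events can also be rated unlikely related, for example when another cause has been identified.
- Section 8.1 describes the comparisons of secondary endpoints between groups as exploratory, and the protocol specifies no comparison of SAE rates.

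Nor can a count be attached. Assuming that 1–5% of patients per arm have such an event in the window gives 0.01 × 75 = 0.75 to 0.05 × 75 = 3.75 patients. The rate has no anchor in the protocol. Placing all of these events in Group A and none in Group B would also require every one to be rated related in A and none in B. It would further require equal event rates on and off drug, which is implausible for blood dyscrasias, since sections 1.2 and 7.6 list blood changes among the drugs' effects.

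**Conclusion.** The point holds as an internal inconsistency between section 7.3 and sections 7.2 and 7.4. It can make SAE classification and 24-hour reporting depend on attributed causality, and on how each site reads the clause, for one narrow class: important medical events that meet none of the five listed outcomes and are rated unlikely related.

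An uneven effect on an SAE tabulation by arm is a possible further consequence. It rests on the literal reading and on ratings that follow drug exposure in study weeks 13–24, and its size is unknown. The recording of adverse events, the severity-and-frequency endpoint, the primary SVR analysis and the sample size are unaffected. The defect is limited, but it sits in an operative safety definition and is worth correcting.

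**What to change.** In section 7.3, replace *a serious adverse drug reaction* with *a serious adverse event*, and make important medical events a sixth item of the SAE list. Keep the existing tests of medical judgment, jeopardy and need for intervention. Leave causality wholly to Table 3. Sections 7.2, 7.3 and 7.4 then share one causality-free definition for both groups, on treatment and in follow-up.

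The cost is a wording amendment, a matching change to the SAE form where it repeats the definition, and a few more 24-hour reports.

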#### **7.4     *Reporting of SAE's***

Any SAE that occurs while treatment or aftercare whether or not deemed drug-related or expected, should be reported within 24 hours after knowledge by the treating physician to his/her local regulatory or drug safety reporting agency (Sponsor Hep-Net) along with a copy to MSD Sharp & Dohme GmbH, Division Pharmacovigilance. Also SAEs, that occur within 30 days after the last application of the study medication or within 30 days after the last medical check-up need to be reported. In case of pregnancy of a female patient in the study or of a female partner of a male patient participating in the study this must be handled in the same way – it must be reported as if it would be an SAE. If the pregnancy affects the female partner of a patient both data about the pregnancy and data about the treatment of the patient are regarded.

In any case the form for Reporting of an SAE is to be filled out and to be faxed to the following addresses within 24 hours after knowledge:

#### **KOMPETENZNETZ HEPATITIS**

Study House  
[name]  
[name]  
[contact]

and

MSD Sharp & Dohme GmbH  
Arzneimittelsicherheit  
[name]  
[name]  
[contact]

The **death** of any subject during the study or within 30 days of study completion (as defined above), regardless of the cause, must be reported to the sponsor Hep-Net and MSD Sharp & Dohme GmbH, Munich, Germany within 24 hours of first becoming aware of the death. If an autopsy is performed, the pseudonymised report must be provided to the sponsor.

#### **7.5     *Management of adverse events***

Management of AEs is generally achieved by dose reduction (see Table 4); however, in the case of life-threatening adverse events, identification of cardiac disease or development of cardiac dysfunction, pregnancy, failure to comply with the requirement for the practice of birth control for both male and female patients, both PegIntron® and Rebetol® therapy should be discontinued permanently.

Upon complete recovery of the adverse event, treatment with interferon alfa-2b and ribavirin may be resumed at a dose that is 50% lower than the dose associated with the adverse event. If this dose is tolerated for at least two weeks, treatment may be resumed at the dose associated with the adverse event. If the adverse event recurs, a reduced, tolerated dose may be administered and maintained or the subject may be taken off the treatment optimization study at the physician's discretion. If a dose reduction is necessary because of an adverse event, the patient must be examined every 2 weeks.

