### **General Remarks**

Unscheduled visits may take place for evaluation of laboratory parameters relevant to clinical safety. An unscheduled visit to monitor hemoglobin will be performed within one week of the patient's last visit if the patient displays a hemoglobin decline which meets all of the following three criteria:

- ⇒ Decline in hemoglobin since the previous visit
- ⇒ Decline in hemoglobin by more than 2 g/dl since the baseline evaluation
- ⇒ Decline in hemoglobin below 11 g/dl.

At the physician's discretion, the patient or a household member will be trained in the subcutaneous injection technique.

Table 4: Rules for dose reductions of PegIntron® and Rebetol®

|                        | Dose reduction                              | Permanent discontinuation of treatment        |
|------------------------|---------------------------------------------|-----------------------------------------------|
| HEMOGLOBIN             | < 10 g/dl
(Rebetol®)                     | < 8.5 g/dl
(Rebetol®)                      |
| WHITE BLOOD CELL (WBC) | < 1.5 X 10  /l
(PegIntron®)  | < 1.0 X 10  /l
(PegIntron®)    |
| GRANULOCYTE            | < 0.75 X 10  /l
(PegIntron®) | < 0.5 X 10  /l
(PegIntron®)    |
| PLATELET               | < 50 X 10  /l
(PegIntron®)   | < 30 X 10  /l
(PegIntron®)     |
| CREATININE             | n/a                                         | > 3.0 mg/dl                                   |
| ALT/AST                | n/a                                         | 2 x baseline and >10 x ULN                    |
| BILIRUBIN-INDIRECT     | > 5 mg/dl (or > 85.5 µmol/l)*
(Rebetol®) | > 4mg/dl (or >68.4 umol/l)
(for > 4 weeks) |
| BILIRUBIN-DIRECT       |                                             | > 2.5 x ULN                                   |

\* Discontinue ribavirin alone for at least 1 week and no more than 2 weeks. Also take a blood sample to determine clotting. If indirect bilirubin falls to < 2.5 mg/dl after ribavirin treatment is interrupted, ribavirin treatment may be restarted at the nearest reduced daily dose stated in the protocol. If bilirubin remains stable at values below 2.5 mg/dl for a period of 4 weeks, ribavirin treatment may be resumed at the full (100%) protocol dose.

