The daily dose is reduced if indirect bilirubin again rises above 4 mg/dl. This dose is then maintained. Treatment may be continued only if indirect bilirubin remains below 2.5 mg/dl. If indirect bilirubin remains high (> 4 mg/dl for more than 4 weeks), PEG-interferon alfa-2b and ribavirin must be permanently discontinued.

If an adverse laboratory event persists that is not severe enough to mandate permanent discontinuation of the drugs, the reduced dose of PEG-interferon alfa-2b or ribavirin (whichever was reduced) may be maintained. If the ribavirin dose was reduced following a decline in hemoglobin to below 10 g/dl, the dose reduction must continue to apply for at least 4 weeks.

The reduced doses may also be maintained if the hemoglobin value is  $\geq 12$  g/dl for women and  $\geq 13$  g/dl for men. If the adverse laboratory event recurs, a reduced, previously tolerated dose may be administered and maintained or the subject may be taken off the treatment optimization study at the physician's discretion.

The dose reduction takes place by lowering the PEG-interferon alfa-2b injection volume and number of ribavirin capsules as described in the tables below. Subjects who develop life-threatening adverse events must have PEG-interferon alfa-2b and ribavirin discontinued definitely.

To ensure that daily dosing is maintained, the dose should be reduced, not the frequency of use.

Table 5: Reduction of Rebetol®

| Initial ribavirin dose | Total number of capsules per day | Reduced dose | Reduced number of capsules per day |
|------------------------|----------------------------------|--------------|------------------------------------|
| 1400 mg/day            | 3-0-4                            | 800 mg/day   | 2-0-2                              |
| 1200 mg/day            | 3-0-3                            | 800 mg/day   | 2-0-2                              |
| 1000 mg/day            | 2-0-3                            | 800 mg/day   | 2-0-2                              |
| 800 mg/day             | 2-0-2                            | 600 mg/day   | 1-0-2                              |

Table 6: Reduction of PegIntron®

| Current dose   | Next dose reduction |
|----------------|---------------------|
| 150 µg         | 120 µg              |
| 135 µg, 120 µg | 100 µg              |
| 105 µg, 100 µg | 80 µg               |
| 90 µg, 80 µg   | 50 µg               |
| 70 µg, 60 µg   | 30 µg               |

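### Section 7.5 gives conflicting rules for the reduced or resumed dose and for indirect bilirubin on re-treatment, so sites could treat the same patient differently

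*Protocol*

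**What the plan says.** All of the text is in Protocol section 7.5 (Management of adverse events, including General Remarks and Tables 4 to 6), except the capsule strength, which is in section 6.1.

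**Reduced and resumed dose**
- The opening of 7.5 says that after complete recovery treatment with both drugs "may be resumed at a dose that is 50% lower than the dose associated with the adverse event". It continues: "If this dose is tolerated for at least two weeks, treatment may be resumed at the dose associated with the adverse event".
- The text before Table 5 says: "The dose reduction takes place by lowering the PEG-interferon alfa-2b injection volume and number of ribavirin capsules as described in the tables below". Table 5 lists one reduced dose for each ribavirin dose, and Table 6 lists the next PEG-interferon dose down (for example "105 µg, 100 µg | 80 µg").
- The footnote to the indirect-bilirubin cell of Table 4 interrupts ribavirin for one to two weeks. Once bilirubin is below 2.5 mg/dl it allows a restart at the closest lower daily dose that the protocol lists, and full dose after four weeks of stable values below 2.5 mg/dl.
- After a fall in haemoglobin below 10 g/dl, a ribavirin reduction has to last at least four weeks.
- Section 6.1 supplies ribavirin as 200 mg capsules.

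**Indirect bilirubin**
- The dose-reduction column of Table 4 reads "> 5 mg/dl (or > 85.5" µmol/l, for ribavirin, with the footnote above.
- The text after Table 4 says that the daily dose is lowered if the value goes above 4 mg/dl again, and that the lowered dose is then kept.
- The next sentence is: "Treatment may be continued only if indirect bilirubin remains below 2.5 mg/dl".
- The permanent stop of both drugs follows: "If indirect bilirubin remains high (> 4 mg/dl for more than 4 weeks"). The permanent-discontinuation column of Table 4 gives the same limit and duration.

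**The concern.** A site that restarts a patient after an adverse event finds a general rule (half the dose), two step tables that almost never give half, and one restart rule that points to the listed doses instead. Nothing says which prevails. A site that sees bilirubin rise again on re-treatment finds two adjacent sentences that point in different directions.

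Patient safety comes first, then consistency of delivered dose across about 30 centres (section 3.1). The protocol itself treats delivered dose as important: entry requires ribavirin above 10.6 mg/kg (section 4.2), and a dose change in the first four weeks or adherence below 80% excludes a patient (section 4.3). Adverse events are a secondary endpoint (section 3.2).

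**Working it through.** **1. Do the table steps reproduce the 50% rule?**

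Inputs: the doses in Tables 5 and 6. Formula: reduction (%) = 100 × (starting dose − reduced dose) / starting dose.

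| Drug | Start | Table dose | Reduction | Half of start |
|---|---|---|---|---|
| Ribavirin (mg/day) | 1400 | 800 | 42.9% | 700 |
| | 1200 | 800 | 33.3% | 600 |
| | 1000 | 800 | 20.0% | 500 |
| | 800 | 600 | 25.0% | 400 |
| PEG-interferon (µg) | 150 | 120 | 20.0% | 75 |
| | 135 | 100 | 25.9% | 67.5 |
| | 120 | 100 | 16.7% | 60 |
| | 105 | 80 | 23.8% | 52.5 |
| | 100 | 80 | 20.0% | 50 |
| | 90 | 50 | 44.4% | 45 |
| | 80 | 50 | 37.5% | 40 |
| | 70 | 30 | 57.1% | 35 |
| | 60 | 30 | 50.0% | 30 |

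One step of 13 equals 50%. No ribavirin step does.

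**2. Can half the ribavirin dose be made?**

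Capsules = (starting dose / 2) / 200 mg.
- 1400 mg: 700 / 200 = 3.5
- 1200 mg: 600 / 200 = 3
- 1000 mg: 500 / 200 = 2.5
- 800 mg: 400 / 200 = 2

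Two of the four doses cannot be halved with whole capsules.

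**3. Does it help to read Table 6 as a ladder taken more than once?**

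Its columns are current dose and next reduction, so repeated use is possible. From 150 µg the rungs are 120, 100, 80 and 50, and half (75) is not among them. Following each start down the table, half is reached exactly only from 100 µg (100, 80, 50) and from 60 µg (60, 30). That is 2 of 9 starting doses, so the ladder reading does not remove the mismatch.

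**4. Time before return to the earlier dose**

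| Rule | Time |
|---|---|
| General rule, opening of 7.5 | at least 2 weeks tolerated |
| Ribavirin reduced after haemoglobin below 10 g/dl | at least 4 weeks of reduction |
| Bilirubin footnote, Table 4 | 4 weeks stable below 2.5 mg/dl |

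**5. Indirect bilirubin**

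Units first: 85.5 / 5 = 17.1 and 68.4 / 4 = 17.1. The two pairs in Table 4 use the same conversion factor, so the limits are not a unit slip.

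Take a patient back on ribavirin after the interruption whose value rises again to 4.5 mg/dl:
- the sentence on a renewed rise: above 4, so lower the dose and keep the lowered dose;
- the following sentence: not below 2.5, so the condition for continuing is not met.

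Both apply to the same patient on the same day.

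Table 4 has a lesser inconsistency: values above 5 mg/dl stand in the dose-reduction column, but the footnote to that cell orders an interruption of ribavirin.

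**The case against.** **Resumption and reduction may be different events.** The 50% rule presupposes a stop and a recovery; the tables describe stepping down, in text about laboratory limits. On that reading, 500 against 800 mg compares a restart with a first step-down. This is the best defence and it may be what was meant, but the protocol does not say so. The bilirubin footnote is a restart after an interruption and uses the listed dose. It could be a specific exception, and the four-week rules could likewise override the two-week rule, but no precedence is given. The capsule problem remains on any reading.

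**The rules are permissive.** Resumption is optional and recurrence is left to the physician. That is why the claim is that sites could differ, not that they would.

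**The two bilirubin sentences might be harmonised.** Keeping the lowered dose could mean only that it is not raised again, with treatment ending if the value fails to drop below 2.5. That needs a time allowance for the drop, which the text does not give.

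**Stronger bilirubin readings.** A reader might infer that limits of 2.5, 4 and 5 mg/dl contradict each other. They need not: 5 can be the first trigger, 4 the limit for recurrence or persistence, and 2.5 the condition for restart. Nor is the range from 2.5 to 4 mg/dl a contradiction for every patient. The 2.5 condition stands in text about re-treatment after the interruption, and not continuing now is compatible with not stopping permanently. Likewise, 4.5 mg/dl for five weeks leads to a permanent stop without passing 5, but one criterion is a level and the other a level with a duration.

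**Conclusion.** The concern holds in two specific places.

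1. The 50% resumption rule and Tables 5 and 6 agree at 1 of 13 starting doses, with no precedence stated. If they are applied to the same patient, they give 500 or 800 mg for 1000 mg ribavirin, and 75 or 120 µg for 150 µg PEG-interferon. The rules on returning to the earlier dose differ as well, two weeks against four.
2. On re-treatment, a renewed indirect bilirubin above 4 mg/dl meets one instruction to reduce and maintain and another that allows continuation only below 2.5 mg/dl. The column heading in Table 4 and its footnote also disagree.

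This rests on the absence of any sentence in section 7.5 that separates or ranks the rules.

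A reader might infer that the conflict distorts the SVR result or the comparison of arms, since Group A has 24 weeks of extension against 12. The protocol does not support a figure for this, as it gives no rate of dose reduction or raised bilirubin. The primary test also compares Group A with a fixed 70% (section 8.1), so a difference in delivered dose between arms would bear on the secondary and exploratory comparisons of A with B. The case for acting rests on patient safety and uniform conduct. The change should be made; it is not a flaw in the statistical design.

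**What to change.** The sponsor should reconcile the opening of section 7.5, the Table 4 footnote, the text after Table 4, and Tables 4 to 6, so that:

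- one rule, with its precedence stated, sets the reduced dose and the resumed dose of each drug at each starting dose, and can be carried out with the capsule and pen or vial strengths in sections 6.1 and 6.2;
- the time before return to the earlier dose is stated once, with any laboratory-specific exceptions named as exceptions;
- one consistent set of indirect-bilirubin instructions covers interruption, reduction, continuation and permanent stop, and the Table 4 column heading matches the action in its footnote.

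The clinical leads decide which rules apply; no dose or limit is proposed here. The cost is amendment wording and a letter to sites, with no effect on sample size or data collection.
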